### 3.3.2 KNOWN POTENTIAL BENEFITS

As Nepal is a cholera endemic country, study participants may receive benefit through OCV vaccination in cholera protection from study participation, but all participants in the study will be closely followed with regular visits and contacts as part of the study procedures. This protocol is not designed to provide treatment for any condition. Participants will have access to their medical records and findings of medical concern will be referred for appropriate care and treatment during the study. The potential benefits to vaccinated participants are substantial, since cholera is endemic in several parts of the world including in Nepal. According to the updated global burden of cholera in endemic countries, it was estimated that over 18 million people, more than 60% of the Nepalese population, are at risk of cholera with an incidence rate of 1.64 per 1,000 resulting in an estimated 30,379 cases annually.

### 3.4. STUDY RATIONALE

Cholera is a disease of inequity that continues to disproportionately affect the world's poorest and most vulnerable people. Endemic in at least 47 countries, transmission of cholera results in an estimated 2.9 million cases and 95,000 deaths per year globally. Nepal is a cholera endemic country and at high risk for outbreaks due to a steady increase in urban population density accompanied by an inadequate supply of safe drinking water and improved sanitation. Most importantly, Nepal faces flooding and landslides during the rainy season every year which often

lead to the breakdown of the already fragile water and sanitation infrastructure making the possibility of cholera outbreaks, which may be challenging to prevent and control.

In 2017 the Global Task Force on Cholera Control launched an ambitious plan of “Ending Cholera: A Roadmap to 2030”, advocating a change in focus from reactive use of vaccine to quell outbreaks to pre-emptive use of OCV integrated with WASH (Water, Sanitation and Hygiene) to systematically prevent outbreaks in high-risk communities. As currently modelled by Gavi, the strategy could avert 66,000–659,000 deaths and 2–27 million cases by 2035 at a procurement cost of \$1.3 billion. However, this strategy requires an estimated 670 million doses of OCV. EuBiologics is the major supplier to the Stockpile, but their current production capacity is ~25 million doses per year. Shanchol™ production is limited to ~4 million doses per year and Shantha has plans to discontinue its commercial sales in 2023. Although other OCV products may enter the market by 2025, the timing and production capacity are unknown. Consequently, the OCV forecast is for continued supply constraint potentially limiting achievement of the WHO objectives for 2030. As Gavi considers OCV moderately cost effective at the current price (~\$1.85 per dose) it has also called for improved value for money in order to sustain or expand their investment.

The manufacturing of the current modified bivalent WC OCVs includes 5 distinct components with two inactivation methods. Redundant heat and formalin inactivated components were included because the relative importance of protein versus polysaccharide antigens in inducing protection was unknown and *Vibrio cholerae* O139, a newly emergent strain at that time, was included under concern that it might become a pandemic pathogen.

Preliminary analyses of the feasibility and impact of simplifying the formulation of the vaccine have indicated that this could decrease the COG by about 20% and increase vaccine production capacity by about 38%, based on the assumption of reducing the number of components to two [formalin inactivated O1 Inaba Phil 6973 (El Tor), O1 Ogawa Cairo 50 (Classical)] and with a re-balanced composition to achieve the same antigenic quantity of O1 Inaba and Ogawa, and to generate an equivalent relevant immune response to support the current label indication (*i.e.*, prevention of cholera caused by *Vibrio cholerae*), and considering removal of strain O139.

## 4. OBJECTIVES

### 4.1 PRIMARY OBJECTIVES

- To demonstrate non-inferiority of OCV-S compared to Shanchol™ as measured by seroconversion rates of anti-*V. cholerae* O1 Inaba and anti-*V. cholerae* O1 Ogawa vibriocidal titer 2 weeks after second dose for all ages (*i.e.*, one lot of OCV-S)
- To assess and compare safety profile in all age strata combined and describe the safety profile in each age stratum 7 days and 28 days after each dose

### 4.2 SECONDARY OBJECTIVES

- To demonstrate non-inferiority of OCV-S compared to Shanchol™ as measured by GMT of vibriocidal titers against *V. cholerae* O1 Inaba and *V. cholerae* O1 Ogawa 2 weeks after second dose (*i.e.*, one lot of OCV-S) for all ages
- To demonstrate non-inferiority of OCV-S compared to Shanchol™ as measured by seroconversion rates of vibriocidal titers against *V. cholerae* O1 Inaba and *V. cholerae* O1 Ogawa 2 weeks after second dose (*i.e.*, one lot of OCV-S) in each age stratum
- To demonstrate non-inferiority of OCV-S compared to Shanchol™ as measured by GMT of vibriocidal titers against *V. cholerae* O1 Inaba and *V. cholerae* O1 Ogawa at 2 weeks after second dose (*i.e.*, one lot of OCV-S) in each age stratum
- To demonstrate the equivalence of immunogenicity as measured by GMT of vibriocidal titers against *V. cholerae* O1 Inaba and *V. cholerae* O1 Ogawa of 3 lots of OCV-S 2 weeks after second dose in adults

### 4.3 EXPLORATORY OBJECTIVES

- To describe the difference of immunogenicity as measured by seroconversion rates of vibriocidal titers against *V. cholerae* O1 Inaba and *V. cholerae* O1 Ogawa of 3 lots of OCV-S 2 weeks after second dose in adults
- To describe vibriocidal antibody responses 2 weeks after first dose for all ages and for each age stratum

## 5. TRIAL ORGANIZATION

The clinical trials in Nepal will be led by IVI, supported by EuBiologics as co-sponsor and manufacturing partner.

## 6. INDEPENDENT ETHICS COMMITTEE/INSTITUTIONAL REVIEW BOARD

Before the investigational product can be shipped to the investigational site and before the enrollment of the first participant, this protocol, the informed consent form (ICF), the assent form (AF), participant recruitment procedures, and any other written information to be provided to participants must be approved by, and/or receive favorable opinion from, the appropriate Independent Ethics Committee (IEC) or Institutional Review Board (IRB) and Regulatory approval.

In accordance with Good Clinical Practice (GCP) and local regulations, each site Principal Investigator and/or the Sponsor are responsible for obtaining this approval and/or favorable opinion before the start of the trial. If the protocol is subsequently amended, approval must be re-obtained for each amendment. Copies of these approvals, along with information on the type, version number, and date of document, and the date of approval, must be forwarded by the site Principal Investigator to the Sponsor together with the composition of the IEC/IRB (the names and qualifications of the members attending and voting at the meetings).

The site Principal Investigators will submit written summaries of the status of the trial to the IRB/IEC annually, or more frequently if requested. All SAEs occurring during the trial that are related to vaccination will be reported by the Investigator to the IRB/IEC, according to the IEC/IRB policy.

## 7. STUDY DESIGN AND CLINICAL PROCEDURES

### 7.1 DESCRIPTION OF THE OVERALL TRIAL DESIGN AND PLAN

#### 7.1.1 TRIAL DESIGN

This is a multicenter, randomized, observer-blinded, controlled study to evaluate immune non-inferiority and safety of OCV-S compared to Shanchol™ in 1 to 40 years old healthy Nepalese participants. Lot-to-lot consistency will be included as a secondary objective. The vaccines will be administered to 2,530 healthy participants. 1,595 participants will be vaccinated with an investigational vaccine (OCV-S) and 935 healthy participants will receive an active control vaccine (licensed Shanchol™). Each participant will be vaccinated with either OCV-S or Shanchol™ twice by 2 weeks apart. Participants will be followed up for 2 weeks after each dose for immunogenicity (blood samples at Day 0, Day 14 prior to first and second vaccination respectively, and Day 28) and for 24 weeks after the second dose for safety assessment. The primary objective is to demonstrate non-inferiority of OCV-S to Shanchol™ as measured by seroconversion rates of vibriocidal titers against *V. cholerae* O1 Inaba and *V. cholerae* O1 Ogawa 2 weeks after second dose for all ages. The secondary objectives are to demonstrate non-inferiority of OCV-S compared to Shanchol™ as measured by GMT and seroconversion rates of vibriocidal titers against *V. cholerae* O1 Inaba and *V. cholerae* O1 Ogawa 2 weeks after second dose for all ages and in each age stratum. The equivalence of immunogenicity will be demonstrated as measured by GMT and seroconversion rates of vibriocidal titers against *V. cholerae* O1 Inaba and *V. cholerae* O1 Ogawa of 3 lots of OCV-S 2 weeks after second dose in adults. Safety profile will be assessed and compared in all age strata combined and described in each age stratum 7 days and 28 days after each dose. Exploratory objective will describe vibriocidal antibody responses 2 weeks after first dose for all ages and for each age stratum. The study has been designed to consider only one lot in the analysis of the primary immunogenicity endpoint in order to reduce the chance that a single consistency lot not meeting the criteria could result in the study not meeting the primary immunogenicity endpoint. To reduce the risk of failing the lot-to-lot consistency objective, it was designed to conduct the lot-to-lot consistency in only adults where immune responses to vaccine may have less inherent variability.

Eligible participants enrolled in the study will be randomized into 4 study groups with age stratum of 1 to 5 years old, 6 to 17 years old, and 18 to 40 years old. Participants will be observed at the study site for 30 minutes after vaccination for safety assessment. Solicited adverse events will be recorded during 7 days after vaccination. Unsolicited adverse events will be recorded during 28 days after first and second doses of vaccination. Serious adverse events will be reported during the entire study period. Blood samples will be collected at baseline prior to vaccination and at 2 weeks post each dose vaccination for immunogenicity assessment (Day 0, Day 14, and D 28). Except for designated study site personnel responsible for vaccine administration, site investigators, study nurse, and those assessing clinical outcomes, as well as data analysts will be blinded to vaccine allocation until data base lock for the statistical analysis.

---

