## 13.2 SAMPLE SIZE

The sample size of the study is calculated to provide about 90% power to show primary Immunogenicity objective of immune non-inferiority of OCV-S to Shanchol™ and secondary immunogenicity objective of immune equivalence of three lots of OCV-S of the study and increased to satisfy total safety population of about N=2,530. The given sample size of N=935 participants per OCV-S and Comparator vaccine group in all ages would provide 99% power to detect the non-inferiority of immunogenicity of OCV-S group (Group C) compared to Shanchol™ (Group D) in terms of seroconversion rate. The assumed seroconversion rate of Shanchol™ is 71% for all ages which is considered in the assumption based on the clinical studies conducted in a neighboring country to Nepal (i.e., India). The sample size of N=330, 360, and 245 participants per OCV-S and Shanchol™ would provide 80% power to detect non-inferiority of OCV-S in terms of seroconversion rates of 75%, 71%, and 84% in adults, adolescents, and young children, respectively. The assumed non-inferiority margin is -10% based on WHO TRS 924. One sided test of non-inferiority is used with significance level of 0.025.

The sample size of N=330 per lot of OCV-S in adults will also provide >90% power for three equivalence tests of GMT ratio of immunogenicity among three lots of OCV-S (A vs. B, B vs. C and C vs. A) with overall two-sided significance level of 0.05. Each of two-sided equivalence test have >90% power to show the equivalence of GMT of immunogenicity of OCV-S with two-sided significance level of 0.05. The equivalence margin of ratio was assumed as [0.5, 2.0] according to precedent study of OCV (i.e., Euvichol®) and other oral vaccine trials, the true GMT ratio is assumed as 1 and the coefficient of variation on titer of immunogenicity is assumed as 2.0. The coefficient of variation of GMT of OCV-S was assumed conservatively based on OCV immunogenicity data. In both sample size calculations, 10% drop out rate is assumed conservatively considering the potential large variation of experience between sites.

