#### 13.6.10 EXPLORATORY ANALYSES

Seroconversion rate of vibriocidal antibody responses against *Vibrio cholerae* O1 Inaba and O1 Ogawa at 2 weeks post second dose of will be calculated by OCV-S (Group A, B, and C in adults) vaccine group. The two-sided 95% CI of seroconversion rate and difference of seroconversion rates will be provided.

Seroconversion rate and GMT of vibriocidal antibody responses at 2 weeks after first dose of OCV-S or Shanchol™ titers against *Vibrio cholerae* O1 Inaba and O1 Ogawa will be calculated. The two-sided 95% CI of seroconversion rate and the difference of seroconversion rates and GMT and ratio of GMTs will be provided by vaccine group for all ages and by age strata.

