| [95% CI]                          |                    |                    |                    | 1.14
[-3.73, 6.01] d,g  | 0.6467 i,g |                    |                    |                    | -1.92
[-5.82, 1.98] d,g | 0.3342 i,g |

Abbreviations: CI=confidence interval; GMT=geometric mean titers; N=number of participants in per-protocol analysis set with non-missing results.

- a The GMT ratio and its 95% CI were calculated as the antilogarithmic of the difference between the mean of the log-transformed data in the test arm and that in the comparator arm with baseline titer adjustment (covariates) in a generalized linear model. Equivalence of GMT ratio between lots of Euvichol-S is confirmed using margin of [0.5, 2.0].
- b The estimated seroconversion rate, 95% CI, and p-values were derived using the generalized linear model (link=identity) for binomial distribution with treatment group as covariate by adjustment for baseline titers. Equivalence of seroconversion rate between lots of Euvichol-S is confirmed using margin of [-10%, 10%].
- c Comparison=GMTGroup C/GMTGroup D
- d Comparison=Group C – Group D
- e Comparisons between Groups A and B
- f Comparisons between Groups A and C
- g Comparisons between Groups B and C
- h The p-value was testing of no significant difference (fold difference=1) in GMT values across the treatment groups using generalized linear model.
- i The p-value was testing of no significant difference (difference=0%) in seroconversion rate across the treatment groups using generalized linear model (link=identity).
- j Comparison across Groups A, B, and C

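### Lot-to-lot equivalence on seroconversion is promised in the design text but is only descriptive in the objectives and in Section 13, which sets no margin or decision rule for it

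*Protocol*

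**What the plan says.** **Narrative sections.** Section 7.1.1 (Trial Design) states: "The equivalence of immunogenicity will be demonstrated as measured by GMT and seroconversion rates of vibriocidal titers against" *V. cholerae* O1 Inaba and Ogawa across three lots in adults. The synopsis Methodology carries the same sentence.

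**Objectives.** The secondary lot objective in 4.2 covers GMT alone: "To demonstrate the equivalence of immunogenicity as measured by GMT of vibriocidal titers against" the two serotypes. Lot seroconversion is in 4.3, among the exploratory objectives: "To describe the difference of immunogenicity as measured by seroconversion rates of vibriocidal titers against" the two serotypes. The synopsis repeats both objectives, so it disagrees with its own Methodology paragraph.

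**Section 13.** Lot GMT is a secondary endpoint (13.1.3) and lot seroconversion an exploratory one (13.1.4). Section 13.2 powers the lots on GMT only: "The sample size of N=330 per lot of OCV-S in adults will also provide >90% power for three equivalence tests of GMT ratio". Section 13.4 states a lot hypothesis, and 13.6.5 a decision rule, for the GMT ratio only, with limits 0.5 and 2.0. For lot seroconversion, 13.6.10 says: "The two-sided 95% CI of seroconversion rate and difference of seroconversion rates will be provided". No margin or rule follows.

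**Appended results.** Note b of Table S3 reads: "Equivalence of seroconversion rate between lots of Euvichol-S is confirmed using margin of [-10%, 10" (the upper limit is 10%). The same note says that the model adjusted for baseline titers.

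**The concern.** The protocol gives one analysis two different standings. If 7.1.1 governs, lot seroconversion is a confirmatory equivalence test, and it lacks the three things such a test needs: a margin, a decision rule and a power statement. If 4.3 and 13.6.10 govern, lot seroconversion is estimated with confidence intervals and no equivalence conclusion may be drawn from it.

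This is more than a slip of wording, because it decides what the trial may conclude about manufacturing consistency. The appended table shows that it matters in practice: it attaches an equivalence verdict to a comparison that the objectives call descriptive. The only 10-point margin in Section 13 is the one-sided −10% for OCV-S against Shanchol, which is a different comparison.

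**Working it through.** **1. The two measures side by side (lots, adults)**

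| Element | GMT | Seroconversion |
|---|---|---|
| Synopsis Methodology, 7.1.1 | equivalence demonstrated | equivalence demonstrated |
| Objective | secondary (4.2) | exploratory, describe (4.3) |
| Endpoint | secondary (13.1.3) | exploratory (13.1.4) |
| Power | >90% (13.2) | none |
| Hypothesis and margin | [0.5, 2.0] (13.4) | none |
| Decision rule | 95% CI inside margin (13.6.5) | none; estimates and 95% CI (13.6.10) |
| Table S3 notes | [0.5, 2.0] (note a) | ±10 points (note b) |

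Only the narrative sentence and note b treat seroconversion as a test. Every operative section describes it.

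**2. Inputs for the power illustration**

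- 330 adults per lot, and "10% drop out rate is assumed conservatively" (13.2): 330 × 0.9 = 297 evaluable.
- Assumed adult seroconversion rate 75% (13.2).
- GMT: coefficient of variation 2.0, true ratio 1, limits [0.5, 2.0] (13.2).
- Two-sided level 0.05 for each lot comparison (13.4), so z = 1.96.
- Assumed here, because Section 13 gives none: a lot margin of ±10 points, taken from Table S3 note b.

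**3. The plan's own figures reproduce**

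- Lot GMT: SD of ln titer = √ln(1 + 2²) = 1.269. SE = 1.269 × √(2/297) = 0.104. Power = 2Φ(ln 2/0.104 − 1.96) − 1, which exceeds 99.9%. The stated figure is >90%.
- Adult seroconversion, OCV-S against Shanchol: SE = √(2 × 0.75 × 0.25/297) = 0.0355. Power = Φ(0.10/0.0355 − 1.96) = 80.4%. The stated figure is 80%.

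**4. Lot seroconversion under the assumed margin**

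- Unadjusted, no true difference, per pair: 2Φ(0.10/0.0355 − 1.96) − 1 = 60.7%. Simulation with 400,000 runs gives 61.0%.
- All three pairs for one serotype, same simulation: 33.6%.
- Without dropout (330 per lot): 68.6% per pair and 42.9% for three pairs.

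**5. Effect of baseline adjustment**

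The unadjusted planning half-width is 1.96 × 3.55 = 7.0 points. The adjusted post-dose-2 intervals in Table S3 are narrower. The widest is Inaba A−C, [−4.10, 5.72], half-width 4.91; the narrowest is Ogawa A−C, [−4.89, 2.74], half-width 3.82. In the same formula, a half-width of 4.91 gives SE = 4.91/1.96 = 2.51 points and power 2Φ(10/2.51 − 1.96) − 1, about 96% per pair. The narrower intervals give more. This is a post hoc figure, not a planned power.

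**The case against.** The best answer is that the operative sections agree with one another. Objectives, endpoints, sample size, hypotheses and analyses all test lots on GMT and describe seroconversion; the conflict comes from one sentence used twice in narrative text. Under 4.3 and 13.6.10 no power is needed, so low power is a defect only if the narrative sentence governs. That stands, and it shows which text to correct. It does not remove the conflict, since the protocol nowhere says which wording prevails.

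Three stronger readings are tempting, and the documents do not support them.

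- **The trial is badly underpowered for lot seroconversion.** The 61% and 34% depend on a margin that Section 13 does not set and on an unadjusted analysis. Section 13.6.10 names no model for this comparison, and with the adjusted precision in Table S3 the per-pair figure is about 96% or more. A figure of about 53% per pair would come from a 71% rate, which 13.2 assigns to all ages and to adolescents; the lots are compared in adults only.
- **The trial could report failed lot consistency.** All six adjusted post-dose-2 intervals in Table S3 lie inside ±10 points.
- **The ±10% margin was invented after the fact.** The SAP is not shown and may contain it. Table S3 belongs to the appended results, not to the plan. All that can be said is that Section 13 does not hold this criterion.

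**Conclusion.** The contradiction holds. The synopsis Methodology and 7.1.1 promise a demonstration of lot equivalence on seroconversion, while 4.2, 4.3 and Section 13 plan one on GMT only. Section 13 gives lot seroconversion no margin, decision rule or power, yet Table S3 note b reports equivalence as confirmed.

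The size is a matter of what may be claimed, not of a known shortfall in power. The figures of about 61% per pair and 34% for three pairs of one serotype are illustrative. They rest on an assumed ±10-point margin, 297 evaluable adults per lot, a 75% rate, no true difference and an unadjusted 95% CI, and adjustment for baseline titer would raise them. The primary non-inferiority objective and the GMT lot-consistency objective are not affected. The point should be corrected because it governs a confirmatory claim.

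**What to change.** Delete *and seroconversion rates* from the lot-equivalence sentence in the synopsis Methodology and in 7.1.1, so that both match 4.2, 4.3 and 13.4. Report lot seroconversion differences with 95% CIs as 13.6.10 already provides, without an equivalence conclusion. If such a conclusion is kept in the results, as in Table S3 note b, label it exploratory and state where its margin was set.

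Adding a margin to 13.4 before unblinding is no longer a workable alternative, because the file already holds results by group.

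The cost is two sentence edits and, where needed, one footnote. The sponsor gives up a confirmatory lot claim on seroconversion.

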#### 7.1.2 TRIAL PLAN

A schedule of assessments is provided in [Table 2. Study Procedures/Schedule of Events](#).

##### 7.1.2.1 VACCINATION

A schedule of study vaccinations is provided in [Table 2. Study Procedures/Schedule of Events](#).

##### 7.1.2.2 VISITS AND CONTACT

Any visit and any procedure must be done after the Informed Consent/ Assent has been obtained.

Evaluation of this investigational vaccine will include medical history, physical examination by the investigators and participant self-assessment. A summary of study procedures and schedule of events is shown in [Table 2. Study Procedures/Schedule of Events](#).

After written consent/assent forms are obtained, screening procedures will be performed as described in the MOP. The screening process will take place during the week prior to enrollment (Days -7 to 0). The study staff will request the screened eligible participants/parent(s)/LAR to visit trial site for vaccination which will be considered as Day 0. A study participant will be enrolled if s/he meets all inclusion and none of the exclusion criteria and the participant's health status is deemed acceptable as determined by medical history, physical examination, and medical judgment of the site investigator. If participant/parent(s)/LAR agrees, screening and enrollment could be done on the same day if screening results are available. A study ID card will be provided to each enrolled participant.

Details of visit procedures are described in Section [7.1.3 Visit Procedures](#)

